### Data management

After completion of blood tests and analysis, nursing staff at the Barnes Clinical Research Facility will be notified and will collect the results from the laboratory. Hard copies of the results will then be stored in a locked, secure area. A member of the CATFISH research team will visit the Barnes Clinical Research Facility at least once every two weeks to collect the results. The results will then be returned to the CATFISH office at the University of Manchester and stored securely.

Once the research team has collected the HbA1c concentration results from the Clinical Research Facility, they will be screened by the CATFISH Research Nurse. If the HbA1c concentration falls outside the normal prediabetes range expected (≥48 mmol/mol), the participant’s general practitioner will be informed by letter of the result. If the concentration remains within the prediabetes range (42–47 mmol/mol) or is within the normal range (<42 mmol/mol) the general practitioner will not be routinely informed of the result. Blood samples for HbA1c testing will be automatically archived after analysis to a secure storage unit in the pathology department at Salford Royal NHS Foundation Trust and kept at 4 °C. They will be kept for a maximum of 2 days and then sent for incineration.

Demographic and outcome data will be collected in an anonymized format using paper-based questionnaires administered face-to-face by the University of Manchester researchers. Additional data about engagement and delivery of the intervention will be captured by the secure and web-based system hosted by NorthWest EHealth at the University of Manchester. Patient confidentiality will be protected throughout all phases of data collection and analysis, in accordance with them UK Data Protection Act, 1998. The data management policy will adhere to Research Councils UK Common Principles on Data Policy and will be created by the principal investigator in accordance with the University of Manchester’s intellectual property policy and relevant third-party agreements. All paperwork will be transferred immediately to the University of Manchester and stored in a lockable fling cabinet. Paperwork with patient-identifiable data (consent form, case report form) should be stored separately from anonymized data (baseline and follow-up questionnaires).

Names and contact details of patients who decide not to take part in the trial will be destroyed by the research team. All other data collected from questionnaires after consent is given will be anonymized. University of Manchester policy on storage of personal data is 5 years after the last publication date of the study or 10 years, whichever is the greater. Consent forms will be retained as essential documents, but items such as contact details will be deleted as soon as they are no longer needed.

### Statistical analysis

We will report the trial and analysis according to CONSORT standards, including full details of use of the various telephone coaching components [43]. The data analyst will be masked to treatment allocation.

For most outcomes, we will present descriptive data on baseline and follow-up scores, to allow assessment of change in IGR2 and IGR3 patients, as well as comparison with outcomes found in pilot evaluations [16, 17]. The focus will be on assessing whether IGR3 achieves at least as good outcomes as IGR2. This will not involve a formal assessment of equivalence.

We will formally test for differences between IGR3 and IGR2 on patient experience using the CSQ-8. Analysis will follow intention-to-treat principles and a pre-specified plan. The core analysis will be via linear regression, using robust standard errors adjusted for the clustering of patients within practices. We will control for baseline values of each outcome and design factors. We will apply multiple imputation to baseline and 9 month variables with missing values by the chained equations approach using scores on all primary and secondary outcome measures (at baseline and follow-up). We will use 20 multiple imputation sets, as this will provide appropriate stability of results. Analyses will be conducted using STATA (version 14) with an alpha significance value of 5 %. We will report standardized effect sizes for all outcomes to aid comparison with published studies.

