### Primary outcome measure

#### Patient experience

Patient satisfaction will be assessed using the Client Satisfaction Questionnaire (CSQ-8), which is a generic survey instrument used widely in primary care clinical trials [32]. The CSQ-8 is an eight-item self-administered questionnaire collected at the end of service delivery and scored using a four-point Likert scale. The CSQ-8 scores range from 8 to 32, with higher values indicating higher satisfaction.

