### Secondary outcome measures

#### Costs of intervention

The costs of delivery of IGR2 and IGR3 will be determined. Hitachi Europe Ltd, with support from Salford Royal Foundation NHS Trust, will provide a detailed cost breakdown of the operation of IGR2 and IGR3, including staff and infrastructure. Data on number and length of calls for each element of the care pathway in each arm will be recorded throughout the trial period. Clinicians responsible for delivery of the intervention will log call times using a standardized activity log pro-forma.

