#### Routine service level data

We will extract data related to a range of processes associated with engagement with and completion of the intervention from the secure web-based intervention hosted by North West EHealth at the University of Manchester. These data will allow us to assess patient fidelity to the pre-specified service model outlined in Table 1. Specifically, we will run queries to produce aggregate data for all patients in the IGR3 arm at the end of the intervention period related to:Completeness of self-assessmentsNumber of times patients logged in to specific pagesNumber of times patients used ‘contact advisor’ option for additional support

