### Participant timeline

The recruitment window runs from July 2015 to the end of June 2016. After consenting and undertaking baseline assessments, participants will enter the IGR3 or IGR2 service, where they will receive active therapeutic contacts for 6 months, followed by a step-down call at 9 months. We will collect measures at baseline, and 9 months (i.e. 3 months after the end of the core contact period; see Table 1). Recruitment flow and timelines of assessments are shown in Fig. 3 and Table 2, respectively.

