At follow-up, the researcher will contact the participant by telephone to arrange a convenient time and place to meet for the follow-up assessment. During this, call the researcher will remind the participant not to tell the researcher if they were part of the telephone-only health coaching group or the web plus telephone health coaching group. At the follow-up assessment visit, the researcher will adopt the same procedures undertaken at the baseline visit to collect and record data on height and weight. The participants will be given the follow-up questionnaire to complete and the researcher will adopt the same procedure undertaken at the baseline visit to ensure that this questionnaire is completed appropriately.

After completing follow-up assessments, participants will be invited to attend an appointment at the Clinical Research Facility at Salford Royal NHS Foundation Trust for a plasma glucose test to measure HbA1c. All blood tests will be conducted by nursing staff at the Barnes Clinical Research Facility, Salford Royal NHS Foundation Trust. Sample type and volume are fluoride oxalate (yellow), 1 ml; the reference range is 3.0–6.0 mmol/l. Laboratory staff will follow the Salford Royal NHS Foundation Trust protocol for prevention and management of potential exposure to blood-borne viruses, including needlestick and sharps injuries [42].

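### The imputation model names predictors that tell it little about the CSQ-8 of people who miss the 9-month visit, and does not clearly include the call records kept in both arms

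*Protocol article*

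**What the plan says.** The Statistical analysis section fixes the imputation in some detail: 20 sets, for baseline and 9-month variables, "by the chained equations approach using scores on all primary and secondary outcome measures (at baseline and follow-up").

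Four other sections determine what those predictors contain for someone who is not seen at 9 months.

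- Patient experience: the CSQ-8 is an "eight-item self-administered questionnaire collected at the end of service delivery", so it has no baseline value.
- Participant timeline: "We will collect measures at baseline, and 9 months". There is no wave in between.
- Data collection: height, weight and the questionnaires share one follow-up visit ("The participants will be given the follow-up questionnaire to complete"). HbA1c comes later still: "After completing follow-up assessments, participants will be invited to attend an appointment at the Clinical Research Facility".
- Costs of intervention, under Secondary outcome measures: "Data on number and length of calls for each element of the care pathway in each arm will be recorded throughout the trial period".

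The web-use data under Routine service level data are described as "aggregate data for all patients in the IGR3 arm at the end of the intervention period". They exist in one arm only and not by participant, so they cannot serve as an imputation predictor for the comparison.

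**The concern.** Multiple imputation improves on a complete-case analysis only when the model holds information on the missing value that the analysis model lacks. Here a non-attender has no follow-up questionnaire score, no weight and, in practice, no HbA1c. What remains is mainly baseline health status, recorded before the participant had met the service that the CSQ-8 rates.

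How far someone got through the coaching is a plausible predictor both of attending at 9 months and of rating the service. Table 1 gives both arms the same call sequence (triage, introduction, action planning, follow-up calls 1–6, step-down), so a count of calls is on a common scale. The protocol's theory of change links engagement, activation and satisfaction, and the Background proposes that the web platform alters engagement. A difference between arms in who drops out is therefore plausible on the trial's own premises. The CSQ-8 is the only outcome for which the protocol promises a formal test between arms, so a shift in that comparison affects the main conclusion.

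**Working it through.** **The plan's own figure.** With 100 per arm and 15% attrition, 85 per arm are analysed. In SD units the standard error of the difference is √(2/85) = 0.153. Power for 0.5 SD at two-sided 5% is 90.0% (noncentral t, 168 df), which reproduces the stated 90%.

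**Assumptions (not in the documents).** Y is the CSQ-8 in SD units, E is call engagement and B is a composite of the baseline scores, all standardized.

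- corr(Y,E) = 0.3 or 0.5.
- corr(Y,B) = corr(E,B) = 0.1, 0.2 or 0.3.
- The chance of missing the visit is logistic in E, with slope 1.0 or 1.5 (lower engagement, more missing).
- There is no true effect.

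**Step 1: how engaged the attenders are.** The mean of E in the full arm is 0. Among attenders, integrating over the logistic model gives:

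| Missing | Slope 1.0 | Slope 1.5 |
|---|---|---|
| 5% | 0.047 | 0.065 |
| 10% | 0.091 | 0.122 |
| 15% | 0.133 | 0.175 |
| 20% | 0.173 | 0.227 |
| 25% | 0.213 | 0.277 |

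**Step 2: complete-case bias in one arm** = corr(Y,E) × mean E among attenders. At 15% missing this runs from 0.3 × 0.133 = 0.04 to 0.5 × 0.175 = 0.09 SD.

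**Step 3: share removed by imputing from baseline scores** ≈ corr(Y,B) × corr(E,B) / corr(Y,E).

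- Baseline correlations 0.1: 0.01/0.5 to 0.01/0.3 = 2–3%.
- Baseline correlations 0.2: 0.04/0.5 to 0.04/0.3 = 8–13%.
- Baseline correlations 0.3: 0.09/0.5 to 0.09/0.3 = 18–30%.

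So 70–98% of the bias remains. A simulation with 400,000 per arm agrees.

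**Step 4: bias in the difference between arms.**

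| Missing by arm | Complete case | Baseline-only imputation |
|---|---|---|
| 15% v 15%, same mechanism | 0 | 0 |
| 10% v 20% | 0.3 × (0.173 − 0.091) = 0.025 to 0.5 × (0.227 − 0.122) = 0.05 | 0.025 × 0.70 = 0.02 to 0.05 × 0.98 = 0.05 |
| 5% v 25% | 0.3 × (0.213 − 0.047) = 0.05 to 0.5 × (0.277 − 0.065) = 0.11 | 0.05 × 0.70 = 0.035 to 0.106 × 0.98 = 0.10 |

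If 15% are missing in each arm but engagement drives this in one arm only, 3,000 simulated trials per scenario give 0.07–0.10 SD (corr(Y,E) 0.5, baseline correlation 0.1, slopes up to 2). The bias favours the arm whose losses are more concentrated among the disengaged.

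**Step 5: effect on error rates** (85 per arm, noncentrality = bias/0.153).

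| Bias (SD) | False positive in the favoured direction (nominal 2.5%) | Two-sided (nominal 5%) |
|---|---|---|
| 0.02 | 3.4% | 5.2% |
| 0.05 | 5.1% | 6.2% |
| 0.10 | 9.5% | 9.9% |

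**Step 6: with E in the imputation model** the bias is about 0 in every scenario above, and the spread of the estimate is unchanged (0.153–0.157 SD). This follows from the set-up: missingness was made to depend on E alone.

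**The case against.** Five points can be made on the other side.

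1. **The plan may not exclude the calls.** A reader might infer that the stated rule shuts them out. The text does not support that: it refers to all secondary outcome measures, and both the call data and health-care use by record linkage are listed under that heading. Neither is naturally a score at baseline and follow-up, so the wording is ambiguous. That ambiguity is what needs settling.

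2. **A separate analysis plan may name auxiliary variables.** It may, and its absence here is no fault. But the article does not leave the predictors open. It states them, and the point concerns that stated choice.

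3. **The baseline scores include the Patient Activation Measure**, which the theory of change treats as a driver of satisfaction. This stands. It is why the working runs to baseline correlations of 0.3, where imputation removes up to 30% of the bias. To say that imputation is the same as a complete-case analysis would hold only at very low assumed correlations.

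4. **Missing a research visit is not the same as leaving the coaching.** University researchers, not Care Call staff, arrange a convenient time and place, and a £20 voucher is offered. This weakens the assumed link but does not remove it.

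5. **A reader might take the near-zero bias in Step 6 as proof of the remedy.** It is not. If satisfaction itself drives non-attendance, beyond what call counts show, bias remains.

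**Conclusion.** The point holds as an improvement to a stated method, not as an error that invalidates the analysis. For people who miss the 9-month visit, the named predictors are mainly baseline health scores, and the call records comparable across arms are not clearly included.

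The size is modest. There is no bias in the difference when dropout and its mechanism are alike in both arms. It is 0.02–0.05 SD at 10% v 20% missing and up to about 0.1 SD in more extreme cases, against a 0.5 SD target and a standard error near 0.15 SD. All of this rests on assumed correlations and dropout patterns, because the protocol gives no dropout by arm.

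Two stronger readings are not supported. One is that the treatment comparison must be biased: individual arm means would be, but the difference is biased only if dropout or its link to engagement differs between arms. The other is that complete call records are held for every participant: the article says calls are recorded in each arm and logged by clinicians on a pro-forma, and completeness by participant is an inference. The planned cost-effectiveness planes and acceptability curves make patient-level records likely but do not establish them.

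**What to change.** State in the analysis plan, before allocation codes are opened, that the chained-equations model includes, where logged, each participant's number of completed coaching calls and whether the step-down call was reached. These enter alongside the stated outcome scores and the design factors, and imputation is done separately by coded arm. State also whether linked health-care use counts among the stated predictors.

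The cost is a sentence or two and a merge of the activity log with the outcome file. No new data are needed, so this remains possible although recruitment has closed.

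There are two small downsides. The log must reach the analyst with arm codes only, so that masking is kept. It is also completed by delivery staff who know the allocation, so its completeness should be tabulated by coded arm before use. The change reduces bias only to the extent that engagement explains missingness, so a sensitivity analysis for data missing not at random remains worthwhile.

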### Sample size

The existing IGR2 service is commissioned for 500 patients per year and we anticipate with the support of Salford Royal NHS Foundation Trust, general practitioners and diabetes specialist nurses to recruit 200 of these patients in 12 months. The trial sample size has therefore been set at 100 patients per arm, based on a pragmatic decision concerning the probable recruitment window. With an estimated 15 % attrition rate, we would have 90 % power to detect an effect on a standardized measure of 0.5 on the CSQ-8, and 70 % power to detect a standardized effect size of 0.4 with a two-sided alpha of 0.05. A significant difference in CSQ-8 scores in favour of IGR3 will prove the hypothesis that the web plus telephone health coaching intervention offers patients a better care experience than the existing telephone-only health coaching intervention.

As a comparison of two active treatments, where one is simply an enhanced version of the other, differences in clinical outcomes, quality of life and cost-effectiveness are expected to be relatively small. Therefore, the trial will not be powered to detect differences for secondary outcomes.

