### Randomization and allocation concealment

On providing consent, participants will be asked to complete baseline assessments and are then randomized using a remote and automated randomization service provided by the Manchester Academic Health Science Centre Clinical Trials Unit (MAHSC-CTU) at the Christie Hospital NHS Foundation Trust, Manchester, UK. To ensure allocation concealment, randomization will be by means of a computer-generated code implemented by a MAHSC-CTU employee and shared by telephone with the Care Call administrator following correct exchange of a password. The Care Call administrator will communicate allocations to Care Call staff (diabetes specialist nurse and health advisors). Participants will be allocated 1:1 to either IGR2 or IGR3 using minimization to ensure balance for age (<40, 40–60, >60 years) and body mass index (≤18.5, 18.6–24.9, 25.0–29.9). We will use minimization with a probability weighting of 0.75 to reduce predictability.

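### The stated imputation predictors leave out randomized arm; applied as written, they shrink the CSQ-8 difference by up to about the missing fraction

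*Protocol article*

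**What the plan says.** The Statistical analysis section of the protocol article describes the imputation in some detail.

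- What is imputed: "We will apply multiple imputation to baseline and 9 month variables with missing values".
- How, and from what: chained equations "using scores on all primary and secondary outcome measures (at baseline and follow-up").
- How many data sets: "We will use 20 multiple imputation sets".

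The analysis model is described just before this: "The core analysis will be via linear regression, using robust standard errors adjusted for the clustering of patients within practices". Its covariates are also given: "We will control for baseline values of each outcome and design factors". The design factors are those in Randomization and allocation concealment, where allocation is made "using minimization to ensure balance for age (<40, 40–60, >60 years) and body mass index".

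The analysis model therefore contains arm, baseline values, age and body mass index, with practice entering through the standard errors. The imputation list contains outcome scores. Body mass index belongs to both, since it is a secondary outcome. Arm and age appear only in the analysis model.

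**The concern.** An imputation model should contain every term of the analysis model, and above all the term being estimated. If arm is left out, the imputed values carry an arm difference only so far as other predictors carry it.

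Here little else would. The CSQ-8 is completed when service delivery ends, so no baseline CSQ-8 is evident. Baseline scores are unrelated to arm because of randomization. Under Data collection, weight and the questionnaires are taken at one follow-up visit, and the HbA1c test is offered only after it. A missed visit will therefore tend to remove most 9-month scores together.

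At stake are the size of the primary CSQ-8 difference, the power given for it, and the standardized effect sizes promised for all outcomes.

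**Working it through.** **Inputs from the documents.** 100 per arm, 1:1 allocation, two-sided alpha 0.05, 20 imputations; "With an estimated 15 % attrition rate" (Sample size). Stated power is 90% at 0.5 SD and 70% at 0.4 SD.

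**Inputs assumed.** CSQ-8 normal with SD 1 and missing completely at random; its correlation with baseline scores is 0 or 0.3; no clustering by practice.

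**1. The plan's own figure.** Analysed per arm: 100 × (1 − 0.15) = 85. Power = Φ(0.5 × √(85/2) − 1.96) = Φ(3.26 − 1.96) = Φ(1.30) = 90.3% (t-test version 90.0%). The 90% reproduces, and it presumes an unbiased estimate. At 0.4 SD the same formula gives 74.1%, not 70%; that gap does not bear on this point.

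**2. Expected attenuation.** Let m be the missing fraction and d the true difference. Observed values differ between arms by d. Values imputed without arm, from predictors unrelated to arm, differ by 0. The completed data then differ by

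(1 − m) × d + m × 0 = (1 − m) × d.

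At m = 0.15: 0.85 × 0.50 = 0.425 and 0.85 × 0.40 = 0.34.

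**3. Simulation.** 1,500 trials per scenario, 20 imputations, Rubin's rules, robust standard errors, no other 9-month data for non-responders, 15% missing:

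| True d | Baseline correlation | Mean estimate, arm omitted | Mean estimate, arm included | Power, omitted | Power, included |
|---|---|---|---|---|---|
| 0.5 | 0 | 0.43 | 0.50 | 83% | 89% |
| 0.5 | 0.3 | 0.43 | 0.50 | 85% | 92% |
| 0.4 | 0 | 0.34 | 0.40 | 60% | 75% |
| 0.4 | 0.3 | 0.34 | 0.40 | 66% | 77% |

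A separate set of 3,000 trials with three baseline covariates, one of them correlated 0.3 with CSQ-8, gave 0.42 and 86% power at d = 0.5 with arm omitted. With correlation 0.3 and d = 0.5, the mean estimate is 0.45 at 10% missing and 0.39 at 20%.

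**4. Standard error.** At d = 0.5, correlation 0.3 and arm omitted, the mean reported standard error is 0.148, while the estimates vary with SD 0.125. With no true difference, the test rejects in 2.2% of trials, against 4.5% with arm included.

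**5. If another 9-month outcome is observed when CSQ-8 is missing.** Assume a correlation of 0.5 with CSQ-8. With an arm effect on that outcome of 0.25 or 0.5 SD, the estimate of a true 0.50 is 0.45 or 0.47. With no arm effect on it, the estimate is 0.42. Including arm, run for the 0.25 case, restores 0.50.

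**6. Cost per unit of satisfaction.** If imputed data feed this ratio and the cost difference is unaffected, full attenuation at 15% missing multiplies it by 1/0.85 = 1.18.

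**The case against.** The strongest reply is that the article never says these scores are the only predictors. It is a condensed account, it refers to a pre-specified plan that is not shown, and a careful analyst may include arm as a matter of course. A reader might infer that the trial has decided to exclude arm; the text does not support that. What remains is that the article does give a predictor list, alongside a separate list of analysis covariates, and the former lacks arm. This is a stated rule that does harm if followed, and not merely a detail left for later.

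Three other inferences should be resisted.

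- *That the design factors are missing altogether.* Body mass index is in the list. Practice is a clustering unit, not a minimization factor. Only age is unnamed.
- *That omitting age shrinks the effect.* It makes the two models inconsistent, but age is balanced by minimization, and its omission does not by itself move the arm difference toward zero.
- *That the full 15% dilution is the expected result.* It is close to an upper bound. Call logs kept by clinicians and record-linked service use do not depend on the follow-up visit, although it is unclear whether they count as scores. Step 5 shows a smaller loss when an observed outcome carries part of the arm effect.

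It is also fair to say that the superiority test errs on the safe side: the pull is toward zero and the standard error is too large. A false claim for IGR3 is not the risk. That is no full defence. For most outcomes, the Statistical analysis section asks whether IGR3 does no worse than IGR2. If those comparisons use imputed data, shrinkage makes a worse arm look similar.

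**Conclusion.** The point holds in conditional form. If the stated list is the whole imputation model, the CSQ-8 difference is attenuated by up to about the missing fraction: 0.50 to about 0.43 SD at 15% attrition, or to about 0.45–0.47 if other 9-month outcomes carrying part of the arm effect are observed. In the full-attenuation case, type I error is about 2% and power at 0.5 SD is about 83–86% against the stated 90%.

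The consequences are a conservative primary test, effect estimates and no-worse-than comparisons biased toward no difference where they rest on imputed data, and a satisfaction difference that is too small for any cost ratio built on it. The figures assume data missing completely at random and no practice clustering. The size is moderate and depends on a plan not shown, so this is a correction to make before analysis and not a fatal flaw.

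**What to change.** State in the analysis plan that the masked treatment-arm code enters every imputation equation, or that imputation is run separately by arm. Add age beside body mass index and the outcome scores. Add practice where feasible: 200 participants over Salford's 47 practices is about 4 per practice (200/47 = 4.3), so a full set of practice terms may not be estimable. Report the complete-case estimate as a sensitivity analysis.

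The cost is one sentence and one line of code. Masking of the analyst is no obstacle, because the regression already needs a coded arm variable. If the pre-specified plan already includes arm, confirming this in writing is enough on that term.
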